### 9.3 Randomization and Stratification

### 9.4 Sample Size and Accrual

###

Viral load set points will be evaluated at 12 and 24 months after completion of the 12 months randomization period, i.e., 24 and 36 months after entry into the study. For each patient, we observe the viral load at the pre-defined times and compare the treated and untreated groups. Based on preliminary studies at Weill Cornell School of Medicine in which the mean viral load set point after stopping HAART was 4.2 log_10_ copies/ml with SD = 0.5 log_10_ copies/mL, we anticipate a standard deviation of 0.5 log_10_ copies/mL for the plasma viral load at the times this endpoint will be measured. This is illustrated in the sample size tables below. Further, based on data from the study by Mellors et al from the MACS, which suggest that a difference of 0.25 log_10_ copies/mL may confer a meaningful long-term clinical benefit, we have evaluated our expected power to detect a difference of this magnitude. Based on these assumptions, we can calculate the number of patients/group that would be required to achieve a given power for detecting a specific measured virologic benefit of TL-HAART:

| Virologic Benefit of TL-HAART | N/group for β=0.80 | N/group for β=0.90 |
| --- | --- | --- |
| 0.25 log_10_ copies/mL | 64 (93, 144)^*^ | 84 (121,189) |
| 0.50 log_10_ copies/mL | 16 (24,36) | 21 (31,48) |
| 0.75 log_10_ copies/mL | 7 (11,16) | 10 (14,21) |

* Power assuming a standard deviation of 0.5 (0.6, 0.75) log_10_ copies/ml of HIV RNA, and α=0.05.

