Thus, with our projected enrollment of 180 subjects, we would have 90 subjects per group which would give us more than 90% power to detect a benefit as small as 0.25 log_10_ copies/mL. If the difference is only slightly greater, we will be able to detect it with β > 0.95. If need be, the sample size could be increased by extending the recruitment period to 30 months rather than 24. If we more conservatively estimate that the standard deviation of the observations of viral load set points will be somewhat larger, e.g., 0.6 or 0.75 log_10_ copies/mL of HIV RNA (as observed by Gallant et al (27) over a longer time period with a more heterogeneous group than we will study), rather than 0.5, then the sample size may still be large enough to detect a difference of 0.25 log_10_ copies/ml of HIV RNA with a power of 0.8. Some would argue that the greatest (and most significant) differences will be present in subjects infected most recently (acute) . It is our intention to recruit 60 such subjects (30/group) in addition to the 120 patients enrolled in the early stage of infection. With this recruitment, the following table shows the power of the study as a function of the expected virologic benefit:

| Virologic Benefits of TL-HAART | Infected 0-2 mo (30/group) | Infected 2-12 mo (60/group) | Infected 0-12 mo (60/group) |
| --- | --- | --- | --- |
| 0.25 log_10_ copies/mL | 35% (26,18)* | 61% (46,32) | 78% (63,45) |
| 0.50 log_10_ copies/mL | 89% (75,56) | 99% (96,85) | > 99% (99,95) |
| 0.75 log_10_ copies/mL | > 99% (98,89) | > 99% (>99,99) | > 99% (>99,99) |

* Power assuming a standard deviation of 0.5 (0.6, 0. 75) log_10_ copies/ml of HIV RNA, and α=0.05.

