If the standard deviation of the viral load set points is 0.5 log_10_ copies/mL, the study is more than adequately powered to detect a difference of 0.25 log_10_ copies/mL unless only a relatively small benefit of treatment is observed only in the acute sub-group. . If the standard deviation is larger, the ability to find a difference of 0.25 log_10_ copies/mL is reduced for this sub-group, but remains high for larger treatment effects. If there is substantial variation in disease progression across individuals, the power will be lower than that given in the table and larger sample sizes would be needed. This is because the variability of the changes includes not only the measurement error associated with the viral load assay but also natural variation in disease progression across individuals (irrespective of whether they are on or off treatment) and/or a differential effect of treatment across individuals. If this were true, the assumed standard deviation of plasma viral load of 0.5 log_10_ copies/mL would be an underestimate. However, it is extremely unlikely that this situation pertains. The standard deviations on which we have based our calculations were observed in real studies in which HAART was discontinued and patients were followed. Therefore, they take into account at least some of the variability in disease course that may pertain to the situation of our study. For this reason, we are quite confident that the protocol we have put forward is feasible and will address the issue for which it is designed.

**Patient Recruitment** - All patients in whom a diagnosis of AIED can be made will be offered the opportunity to participate in the study. Over two years, we will recruit 180 patients into the protocol, including significant numbers of IDUs, including 48 in Baltimore and 132 at Canadian sites (overall, 1-2/week in all the sites combined).

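### The second power table in Protocol 9.4 does not give the power of the planned 30, 60 and 90 per group; its entries fit 20, 40 and 60 and understate power

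*Protocol*

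**What the plan says.** Section 9.4 sets total enrolment at 180, made up of 60 acute subjects (30 per group) and 120 early subjects (60 per group). For the whole study it states that "we would have 90 subjects per group which would give us more than 90% power to detect a benefit as small as 0.25" log10 copies/mL. That difference is chosen because "a difference of 0.25 log_10_ copies/mL may confer a meaningful long-term clinical benefit". On variability, "we anticipate a standard deviation of 0.5 log_10_ copies/mL for the plasma viral load". The second table's footnote adds 0.6 and 0.75 as alternatives in brackets and sets alpha: "Power assuming a standard deviation of 0.5 (0.6, 0. 75) log_10_ copies/ml of HIV RNA", with α=0.05.

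The second table is introduced as the power that follows from this recruitment. Its heads are 30/group (0-2 months), 60/group (2-12 months) and, for all patients, "Infected 0-12 mo (60/group"). The 0.25 log10 row reads 35% (26,18), 61% (46,32) and 78% (63,45).

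The next paragraph says that at SD 0.5 "the study is more than adequately powered to detect a difference of 0.25" log10 copies/mL. It makes one exception, for a small benefit seen only in the acute sub-group.

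**The concern.** Two problems show without any calculation. First, 30 + 60 is 90, not 60, so the all-patient head does not match the recruitment that the table claims to describe. As a result, section 9.4 gives two powers for the primary comparison at the difference it calls meaningful: more than 90% in the text and 78% in the table. Second, two columns are both headed 60/group, yet they show 61% and 78% for the same effect, SD and alpha. Both cannot be right.

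Section 9.6 plans treatment comparisons within the acute and early strata, and this table is the only statement of their power. A reader who takes it at face value will misjudge what a null result in either stratum means, and may think the primary comparison weaker than it is.

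**Working it through.** **Inputs, all from section 9.4.** Differences d = 0.25, 0.50 and 0.75 log10; SD = 0.5 (0.6, 0.75); alpha = 0.05; equal groups; planned n per group 30 (acute), 60 (early) and 90 (all). Sidedness is not stated.

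**Step 1: confirm the method on the first table.** The formula is n per group = 2(z₀.₉₇₅ + z_power)² SD²/d². For d = 0.25 and SD 0.5 (0.6, 0.75):

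- 80% power: 63 (91, 142), printed 64 (93, 144).
- 90% power: 85 (122, 190), printed 84 (121, 189).

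All entries of that table reproduce within 2 patients with a two-sided test. A one-sided test gives 50 and 69 for the SD 0.5 entries and does not fit.

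**Step 2: compute the second table at the planned sizes.** Power = Φ(d / (SD·√(2/n)) − 1.96). For d = 0.25 and SD 0.5:

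- n = 30: 0.25/(0.5 × 0.2582) = 1.936; Φ(−0.023) = 49.1%
- n = 60: 0.25/(0.5 × 0.1826) = 2.739; Φ(0.779) = 78.2%
- n = 90: 0.25/(0.5 × 0.1491) = 3.354; Φ(1.394) = 91.8%

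| 0.25 log10, SD 0.5 (0.6, 0.75) | Printed head | Printed power | Power at printed head | Power at planned n |
| --- | --- | --- | --- | --- |
| Acute | 30 | 35 (26, 18) | 49 (36, 25) | 30: 49 (36, 25) |
| Early | 60 | 61 (46, 32) | 78 (63, 45) | 60: 78 (63, 45) |
| All | 60 | 78 (63, 45) | 78 (63, 45) | 90: 92 (80, 61) |

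The acute and early entries fail against their own heads. The all-patient entry agrees with its head, but the head is not the plan.

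**Step 3: find which sizes the printed entries fit.** A search over n = 10 to 120 per group on the 0.25 and 0.50 rows gives best fits of 20, 40 and 60.

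| n per group | 0.25 log10: computed / printed | 0.50 log10: computed / printed |
| --- | --- | --- |
| 20 | 35.2 (26.0, 18.3) / 35 (26, 18) | 88.5 (75.0, 55.9) / 89 (75, 56) |
| 40 | 60.9 (46.2, 31.9) / 61 (46, 32) | 99.4 (96.1, 84.6) / 99 (96, 85) |
| 60 | 78.2 (62.6, 44.7) / 78 (63, 45) | >99.9 (99.5, 95.5) / >99 (99, 95) |

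The 0.75 row agrees too (n = 20: 99.7, 97.7, 88.5 against >99, 98, 89). Every entry is within one point.

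**Step 4: try other explanations.** For 30, 60 and 90 per group at 0.25 log10 and SD 0.5:

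- The t-test gives 47.8, 77.5 and 91.6%.
- One-sided tests move further away (61.5, 86.3 and 95.6%).
- A smaller two-sided alpha does not fit all three columns: 0.025 gives 36.4, 68.0 and 86.2%; 0.01 gives 24.4, 54.9 and 77.2%.
- A uniform loss of one third would turn 30/60/90 into 20/40/60. Section 9.4 states no such loss, and it would contradict both the heads and the claim of more than 90%.

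**The case against.** The strongest case on the other side is that little depends on this table. The sample size rests on the first table (84 per group for 90% power at SD 0.5) and on the sentence about 90 per group, and both reproduce. The primary endpoint is the all-patient comparison, whose power is stated correctly in the text. The stratum comparisons are subgroup analyses, backed in section 9.6 by a formal treatment-by-stage interaction analysis. The printed powers err on the low side. All of this stands, and it limits the weight of the point.

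Four stronger readings are tempting, and the protocol does not support them.

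- **That no column matches its head.** The third does: 78% (63, 45) is correct for 60 per group.
- **That the table survives from an abandoned 120-patient design.** The fit to 20/40/60 suggests a calculation for 120 patients, but the protocol does not say where the numbers came from.
- **That the paragraph after the table is simply false.** It speaks of the study as a whole, which at 90 per group has about 92% power at SD 0.5. The fair criticism is that its single exception leaves out a 0.25 log10 benefit confined to the early stratum.
- **That neither stratum can reach 80%.** The figures here are unadjusted, whereas section 9.6 adjusts for baseline viral load and CD4 count. The protocol gives no baseline correlation. As an assumption, if baseline explains a fraction R² of the variance, the early stratum reaches 80% when 1 − R² = (2.739/2.802)² = 0.956, so R² of about 0.05 suffices. The acute stratum would need 1 − R² = (1.936/2.802)² = 0.48, so R² of about 0.52. The early shortfall is borderline; the acute one is not.

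**Conclusion.** The point holds as an internal inconsistency in the power statement, of limited consequence. At 0.25 log10 and SD 0.5 the printed powers fall short of those for the planned sizes by 14 points (acute, 35 against 49), 17 points (early, 61 against 78) and 14 points (all patients, 78 against 92). The acute column is also wrong at 0.50 log10, where it prints 89% (75, 56) against 97% (90, 73). These figures assume a two-sided test at 0.05, equal groups, no loss to follow-up and no baseline adjustment; the t-test changes them by little more than a point.

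Because the error understates power, it gives no reason to question the 180 subjects or the claim of more than 90% power.

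**What to change.** Recompute the second table for 30, 60 and 90 per group and change the last head to 90/group. Unadjusted, two-sided alpha 0.05, SD 0.5 (0.6, 0.75):

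| Benefit | Acute, 30/group | Early, 60/group | All, 90/group |
| --- | --- | --- | --- |
| 0.25 log10 | 49% (36, 25) | 78% (63, 45) | 92% (80, 61) |
| 0.50 log10 | 97% (90, 73) | >99% (>99, 95) | >99% (>99, 99) |
| 0.75 log10 | >99% (>99, 97) | >99% (>99, >99) | >99% (>99, >99) |

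State in the footnote that the test is two-sided. Amend the paragraph after the table to say that, at SD 0.5, power for 0.25 log10 is about 92% overall, but about 78% if the benefit is confined to the early stratum and about 49% if confined to the acute stratum, before any gain from baseline adjustment.

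The cost is a text correction. Enrolment, procedures and analyses do not change.

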### 9.5 Monitoring

The Data Safety and Monitoring Committee of the Canadian Trials Network will serve as the DSMB for this study. The study will be reviewed every six months.

HAART associated toxicity will be assessed as follows:

- Toxicity leading to treatment discontinuation
- Evaluation of Serious Adverse Events
- Evaluation of grade 3 and 4 Adverse Events

Viral load and T-cell data in the treated versus untreated groups will be compared.

### 9.6 Analyses

Primary Endpoint

 The 24 month log plasma viral load will be compared between allocated groups on an intent-to-treat basis using linear regression to adjust for baseline plasma viral load and CD4 lymphocyte count.  All patients who have at least one post baseline visit will be included in the analysis. Patients who withdraw from follow-up prior to 24 months will have their 24 month viral load estimated using regression techniques based on group and individual trajectories.  Secondary sensitivity analyses using other analytic strategies including last observation carried forward will be used to assess the robustness of the result.

 Secondary Endpoints

Between group comparison of log plasma viral load at 36 months, and CD4 lymphocyte count at 24 and 36 months will be conducted in the same way as the analysis of 24 month viral load.

Subgroup analyses comparing treatment groups on the CD4 lymphocyte count and plasma viral load outcomes at 24 and 36 months will be carried out similarly, focusing (a) on patients treated in the acute stage and (b) patients treated early.

 A further analysis for each of the endpoints will be done using baseline CD4 lymphocyte count and plasma viral load, stage of disease, the interaction of stage and treatment, and treatment as predictors of outcome in a linear regression analysis.  This additional analysis is being done to perform formal statistical assessment of whether there are treatment by stage interactions. (The presence of an effect in one subgroup, and the lack thereof in another does not necessarily imply that the difference between the result in the two strata is statistically significant).

The toxicity of HAART will be presented using descriptive statistics as follows:

(a) percentage of patients discontinuing therapy because of toxicity

(b) percentage of patients suffering a serious adverse event (SAE)

(c) percentage of patients suffering a grade 3 or 4 adverse reaction

 All adverse events, including minor adverse events will be classified using the ACTG template.

 Confidence intervals around the percentages will be calculated.

##

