### 1.2 Primary Objective

To compare the steady state viral load (plasma HIV RNA concentration) in patients who have received TL-HAART to that achieved in similar patients who did not receive any antiretroviral treatment.

###

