**The principal study endpoint will be a comparison of the plasma viral load (plasma HIV RNA concentration) 24 months after initial presentation in treated vs. untreated patients.** Additional study endpoints will be: The plasma viral load 36 months after initial presentation in treated vs. untreated patients; the CD4 lymphocyte count 24 and 36 months after initial presentation in treated vs. untreated patients; The plasma viral load and CD4 lymphocyte count 24 and 36 months after initial presentation in patients treated in the acute vs. early stage of infection (this is the parameter that was the basis for the calculations of the study’s power); the need to initiate (or re-initiate, for those who were in the treatment arm) HAART over the period of observation in all treated vs. untreated patients; toxicity of HAART in all treated patients.

Those who decline to participate in the study or do not meet the inclusion criteria will be excluded from this study and will be given referrals to local care providers with expertise in treating HIV infection.

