## 5.0 STUDY TREATMENT (OR INTERVENTION)

5.1 Regimens, Administration, and Duration

All antiretroviral drugs to be used within this protocol will be licensed for sale for the treatment of HIV infection in Canada and the United States at the time and place at which they are used. (Table A) They will be prescribed and administered according to the version of the DHHS guidelines that are current at the time treatment is given. In Canada, all medications are 100% reimbursed by provincial drug plans. We will use once daily dosing and directly observed therapy (DOT) when appropriate. In Baltimore, most of the medications will be donated by pharmaceutical companies, or will be available free of charge from the MADAP program of the state of Maryland, or will be paid for by patient’s insurance. Study funds will be available to cover co-payments for drugs purchased through patient’s insurance. Combinations of two nucleoside/nucleotide analogues and a third or fourth agent will be used in all cases. (Note: ritonavir used for the purpose of boosting another protease inhibitor will not be considered an additional agent) As new drugs become licensed, they will be available to be used in this protocol. All patients who are randomized to receive HAART will have treatment discontinued after twelve months of therapy unless there is a medical contraindication to doing so, such as chronic HBV infection, CD4 cell count < 350 cells/mm^3^, or pregnancy. Patients who are receiving a non-nucleoside reverse transcriptase inhibitor will substitute a protease inhibitor (with or without ritonavir boosting) for 2-4 weeks prior to discontinuation of the entire regimen, if this is judged to be appropriate by the study physician.

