6.1.2 On-Study Evaluations

Study visits must be scheduled on the weeks indicated in the schedule of events with a window period of:

- 7 days on each side of target date (first year of study)
- 14 days on each side of target date (all subsequent visits)

6.1.3 Evaluations for subjects randomized to HAART who do not start study treatment.

Subjects who do not initiate study treatment within 24 hours of randomization will be reevaluated at week 1 to determine the circumstances that have led to this delay in beginning their therapy.

6.1.4 Evaluations for subjects not randomized to HAART who initiate or re-initiate study treatment

for clinical or immunologic reasons.

Subjects will be seen two weeks after initiation of therapy, and monthly until HIVRNA <50 copies/mL. After this they will follow their original visit schedule.

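### The primary analysis lets month-24 viral loads measured on HAART stand as set points, although the objective and the sample size concern viral load off treatment

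*Protocol*

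**What the plan says.** **Objective and sizing.** Protocol section 1.2 compares the steady-state viral load after TL-HAART with that in "similar patients who did not receive any antiretroviral treatment". Section 9.4 treats the month-24 value as a set point: "Viral load set points will be evaluated at 12 and 24 months after completion of the 12 months randomization period". Its planning mean (4.2 log10) and SD (0.5 log10) come from patients who had stopped HAART.

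**Analysis.** Section 9.6 states: "The 24 month log plasma viral load will be compared between allocated groups on an intent-to-treat basis". On who is included: "All patients who have at least one post baseline visit will be included in the analysis". The only replacement rule is for loss to follow-up: "Patients who withdraw from follow-up prior to 24 months will have their 24 month viral load estimated". The sensitivity analyses include last observation carried forward; none is tied to HAART use.

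**HAART at month 24.** Section 3.0 lists as an additional endpoint "the need to initiate (or re-initiate, for those who were in the treatment arm) HAART over the period of observation". Section 6.1.4 covers patients who begin HAART for clinical or immunologic reasons: "Subjects will be seen two weeks after initiation of therapy, and monthly until HIVRNA <50 copies/mL", after which they return to their original schedule. Footnote 7 of Appendix II applies the same rule to initiation and re-initiation. Section 5.1 stops TL-HAART at month 12 "unless there is a medical contraindication to doing so, such as chronic HBV infection", CD4 below 350 or pregnancy.

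**The concern.** A month-24 viral load drawn on effective HAART shows that the drugs are working. It does not show what a completed one-year course left behind. Under section 9.6 a control patient who progressed, started HAART and was suppressed by month 24 would score as an excellent set point. So would a TL-HAART patient who could not stop at month 12. Neither value bears on the question in section 1.2.

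The error need not cancel between arms. The hypothesis in section 1.1 is that TL-HAART reduces or delays the need for HAART. If that is true, controls will tend to use more HAART by month 24, their mean will fall, and the analysis will work against the effect the trial is looking for. In the other direction, continuation past month 12 can occur only in the TL-HAART arm and would imitate a lasting benefit. Even with equal use, a mixture of suppressed and unsuppressed values is far more variable than the SD of 0.5 used for sizing.

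**Working it through.** **Inputs.** From section 9.4: off-treatment mean 4.2 and SD 0.5 log10, target difference 0.25 log10, alpha 0.05 (taken as two-sided). From section 9.4 as well: 90 patients per group. On-HAART level: 50 copies/mL, the suppression threshold in section 5.2, so log10(50) = 1.70. Milder case: 400 copies/mL, also a threshold in section 5.2, so log10(400) = 2.60. The share of each arm on HAART at month 24 is not given; the values below are assumptions.

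**The plan's own figures.** n per group = 2 × SD² × (z for alpha + z for power)² / difference².
- 80% power: 2 × 0.25 × (1.960 + 0.842)² / 0.0625 = 62.8, so 63 (64 with the t-test). The protocol has 64.
- 90% power: 2 × 0.25 × (1.960 + 1.282)² / 0.0625 = 84.1, so 85 (86 with the t-test). The protocol has 84.
- Power with 90 per group: 0.25 / (0.5 × √(2/90)) = 3.354, and Φ(3.354 − 1.960) = 91.8%. The protocol says more than 90%.

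The sizing reproduces, on the premise that every month-24 value is off HAART.

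**Shift from unequal use.** If a share p of an arm is on HAART, the arm mean falls by p × gap.
- At 50 copies/mL: gap = 4.20 − 1.70 = 2.50. A 10-point difference gives 0.10 × 2.50 = 0.25 log10, the whole target. That is 9 of 90 patients.
- At 400 copies/mL: gap = 4.20 − 2.60 = 1.60. The same shift needs 0.25 / 1.60 = 15.6 points, about 14 of 90.

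Example with a true benefit of 0.25, 10% of TL-HAART and 20% of controls on HAART at 50 copies/mL:
- TL-HAART mean = 0.9 × 3.95 + 0.1 × 1.70 = 3.725.
- Control mean = 0.8 × 4.20 + 0.2 × 1.70 = 3.700.
- The benefit has vanished (−0.025), and the chance of a significant benefit is about 2%.

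With no true effect, 20% of TL-HAART against 10% of controls gives a false benefit of 0.25, significant in about 39% of trials. Reversing the shares gives a false harm with the same probability.

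**Variance from equal use.** With share p in an arm, variance = (1 − p) × 0.5² + p(1 − p) × gap². For controls at p = 0.10: 0.225 + 0.09 × 6.255 = 0.788, SD 0.89. In the TL-HAART arm with a true benefit of 0.25 the gap is 2.25 and the SD is 0.83. The observed difference is 0.9 × 0.25 = 0.225, with standard error √((0.788 + 0.681)/90) = 0.128. Power is Φ(1.761 − 1.960) = 42%.

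| On HAART, each arm | Control SD (50 copies/mL) | Power (50 copies/mL) | Control SD (400 copies/mL) | Power (400 copies/mL) |
|---|---|---|---|---|
| 0% | 0.50 | 92% | 0.50 | 92% |
| 5% | 0.73 | 61% | 0.60 | 78% |
| 10% | 0.89 | 42% | 0.67 | 64% |
| 20% | 1.10 | 25% | 0.78 | 44% |

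These are unadjusted normal tests. The covariate adjustment in section 9.6 is left out. It could trim the off-HAART variance, but baseline covariates cannot remove a shift caused by HAART taken after randomization.

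**The case against.** **Intent-to-treat is defensible, and the trial tests a strategy.** The Schema and section 2.2.1 both say a strategy is being tested, and the need for HAART and progression to CD4 below 350 are assessed separately. A reader might infer that intent-to-treat is itself the mistake; the documents do not support that. Comparing patients as randomized is sound. The fault is the value entered for those on HAART, because suppression by ongoing drug is not the lasting benefit of a one-year course. The separate endpoints do not correct the primary one.

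**Section 9.6 never mentions on-HAART values.** True; their inclusion follows from its wording and is not declared. But the section itself fixes the population, the model and the one replacement rule, and on-HAART patients fall inside the first and outside the last. A statistical analysis plan might add a rule, but the protocol's stated analysis misses its objective. Last observation carried forward does not help, because these values are observed, not missing.

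**The size is unknown.** This stands. A reader might infer that many patients will be suppressed at month 24, or that the power is lost. The protocol gives no rate, and section 4.2.2 excludes patients with two CD4 counts below 350 at entry. At 5% per arm the SD of 0.73 is still inside the 0.75 that section 9.4 tabulates. The most alarming null case (10% of TL-HAART and no controls on HAART, a false benefit in about 64% of trials) assumes no control starts HAART, which sits badly with a protocol that provides for it.

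**Conclusion.** The concern holds. Followed as written, section 9.6 places viral loads measured on HAART in a comparison that sections 1.2 and 9.4 define and size as off-treatment set points. HAART use can decide the result; the documents do not show that it will.

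The scale rests on three assumptions: off-treatment values as in section 9.4, a fixed on-HAART level, and assumed shares on HAART. Within these, an imbalance of 10 to 16 points is worth the entire target effect, in either direction. Balanced use does not bias the null comparison, but it dilutes a true effect and inflates the variance, with a material loss of power from as little as 5% per arm. This should be settled before the primary analysis is run.

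**What to change.** Amend section 9.6 as follows.

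1. State that a month-24 viral load drawn on HAART is not used as a set point.
2. For those patients, estimate the off-HAART month-24 value with the regression on group and individual trajectories already planned for withdrawals. Use only off-HAART measurements: untreated values in controls, and values after stopping in the TL-HAART arm. Keep all randomized patients in the comparison.
3. Add a prespecified sensitivity analysis that ranks as worst every patient on HAART at month 24 for clinical or immunologic reasons, whether started, restarted or never stopped, by the same rule in both arms.
4. Report HAART use at month 24 by arm and reason, with the as-observed intent-to-treat comparison alongside.
5. Handle HBsAg-positive patients in a sensitivity analysis defined by the screening result. Do not remove them from the primary set; section 9.0 says every randomized patient will be evaluated.

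Making the worst-rank comparison primary would go further than needed: the endpoint and sizing in section 9 rest on a mean log10 difference.

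**Cost.** No new data are needed: section 6.2.3 records HAART changes and Appendix II has HBsAg at screening. The price is reliance on a model, and the power statement in section 9.4 should be rechecked for it. The model is weakest for TL-HAART patients who never stopped, who have no post-treatment value and can be estimated only from their group. Footnote 6 of Appendix II lists viral load at months 18, 24, 30 and 36, so early restarters will also have few off-HAART values. The worst-rank analysis depends on open-label decisions to start HAART, which is why it is supportive only.
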